#### 2.8.2. Verum Acupuncture Group 1 (VA1)

Participants assigned to the VA1 will receive 12 acupuncture sessions over 4 weeks, that is, 3 days/week. A telephone interview will take place two weeks after the end of treatment to collect data on the severity of pruritus symptoms, amount of TCS used, and adverse effects. Participants' final visit will occur 4 weeks after the end of treatment. No other intervention will be permitted during the study period.

#### 2.8.3. Verum Acupuncture Group 2 (VA2)

Participants assigned to the VA2 will receive 8 acupuncture sessions over 4 weeks, that is, 2 days/week. A telephone interview will be given two weeks after the end of treatment to collect data on the severity of pruritus symptoms, amount of TCS used, and adverse effects. Participants' final visit will occur 4 weeks after the end of treatment. No other intervention will be permitted during the study period.

#### 2.8.4. Sham Acupuncture Group (SA)

Participants assigned to the SA group will receive 8 acupuncture sessions over 4 weeks, that is, 2 days/week. Sham acupuncture treatment will be conducted on 6 control points: a point 1 to 2 cm proximal and 1 cm medial to LI7, a point 1 cm proximal and 1 cm medial to LI11, and a point 1 cm proximal and 1 cm lateral to ST36, each bilaterally. Instead of intradermal needles, the same sized stainless steel rings without needles, that is, nonpenetrating intradermal needles, which were designed and validated for blinding for our study, will be attached to three control points: a point 1 cm proximal and 1 cm medial to LI11, bilaterally, and finger point in the ear, contralaterally [25]. Unlike VA1 and VA2, fixed acupuncture treatments will be given, but questions about symptoms, TCS, and adverse effects will be asked to participants in this group. A telephone interview will also be given two weeks after the end of treatment to collect data on the severity of pruritus symptoms, amount of TCS used, and adverse effects. After the 4-week treatment period, participants will return for a final visit at 4 weeks after the end of treatment, identical to VA1 and VA2.

### 2.9. Compliance and Discontinuation

During the study period, each patient will receive either 12 or 8 treatment sessions according to their group assignment. Since frequent hospital visits may be the burden to participants and may induce them to withdraw from the trial, we identified a minimum number of treatments to be considered compliant, as follows: at least 10 sessions of 12 should be completed for VA1, and at least 6 sessions of 8 should be completed for VA2 and SA. For dropouts who did not fulfil the aforementioned compliance criteria, last available data will be taken for the analysis.

The study coordinator will maintain regular contact and encourage participants to complete all treatment sessions and follow-up visits. Should a participant withdraw consent, any data collected from the participant will be kept in files safely for 3 years and then will be discarded.

### 2.10. Outcome Measures

One research nurse who is otherwise not involved in this study will conduct a series of outcome measures: its schedule is depicted in Table 2. There will be no separation between primary and secondary outcomes since it is an exploratory study to evaluate the independent effectiveness of acupuncture to treat AD and to collect outcome data for further study.

Participants with AD will complete all the outcome measures; healthy controls will submit to blood collection and complete the Cold-Heat, Centre for Epidemiologic Studies-Depression Scale (CES-D), and state-trait anger expression inventory (STAXI) questionnaires.

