### 2.2. Hypotheses

Acupuncture treatment will mitigate pruritus and other symptoms of AD and will improve quality of life in patients with AD, compared with sham acupuncture.Three times weekly acupuncture treatment over one month will produce better outcomes than twice weekly acupuncture treatment over one month.Certain biomarker levels might be affected by the therapeutic effect of acupuncture and/or development of AD.

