### 2.11. Statistical Methods

#### 2.11.1. Sample Size Calculation

The proposed study is a RCT whose primary aim is to investigate the feasibility to recruit and treat participants with AD with acupuncture and to evaluate acupuncture's antipruritic effects. We will calculate the effect sizes of key outcomes including itch VAS and SCORAD index, to inform power calculations for a further large-scale study. A total of 30 individuals with AD and 20 healthy controls will be recruited during the study period; participants with AD will be randomly assigned in a 1 : 1 : 1 ratio to one of two active acupuncture regimens or sham acupuncture. Healthy controls will not receive any treatment. Considering an estimated 20% dropout rate, we identified the sample size with the advice of a statistician. The statistical significance level will be set at 0.1 considering the applied small size.

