#### 2.11.2. Statistical Analysis Plan

We will perform descriptive analyses for all outcome measures. Categorical variables will be provided with percentages, and continuous variables will be provided as means with standard deviations. An independent statistician will perform statistical analyses using SPSS 21.0 (IBM SPSS Statistics, New York, USA). Missing data will be replaced by carrying forward the most recent nonmissing value, and the time and reason for the missing data will be recorded. Depending on the recorded reasons, multiple imputation by an independent statistician will be done and compared.

The effectiveness of the intervention will be provided by examining changes in outcome measures between baseline and end of treatment and through the follow-up period, using a repeated measures analysis of variance (ANOVA) and *χ*^2^ test. The difference in effect between VA1 and VA2 will be analysed by examining changes in the itch VAS and SCORAD index, by the Mann–Whitney *U* test on continuous variables and *χ*^2^ test on categorical variables. The difference in therapeutic effect between VA (using the most efficacious dose between VA1 and VA2) and SA will be investigated in the same way. The data will be analysed with a *p* = 0.1 (two-sided) statistical significance level and 90% confidence intervals will be provided following the statistician's advice for a small sample size. The current data will be used to calculate the number of participants needed to reach a significance level of 0.05 and 80% power.

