## 3. Discussion

A recent systematic review failed to identify any RCTs on acupuncture as treatment for AD, as it has not been extensively researched [15]. We describe a protocol for a randomised, sham-controlled feasibility trial comparing two VA groups with different treatment schedules with SA to assess the effectiveness of acupuncture in individuals with AD, to be conducted in clinical settings in Korea. The aims are to evaluate whether the proposed acupuncture treatments warrant further investigation for improvement of symptoms, mental health, and quality of life and whether a relationship can be established between certain biomolecules and the development of AD by comparing levels in the blood of individuals with AD to healthy controls.

Determining an optimal dose of acupuncture treatment involves complex decision making [68, 69]. Clinical practice and patients' acceptability should be carefully considered when comparing two different dosages/schedules (3 days weekly versus 2 days weekly for 4 weeks). Our study results will elucidate which regimen produces maximal effectiveness and which schedule participants prefer, which is of importance to practitioners and educators.

We will limit enrolment to individuals with mild to moderate AD. Since KMDs usually treat severe cases with more intensive combinations of treatment, such as acupuncture and herbal medicine or acupuncture and hospitalisation, we selected acupuncture alone in order to detect differences between treatments without introducing other confounders; in addition, rescue medication will be permitted as we believe that this strategy reflects real world practice.

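### No outcome, time point or contrast is ranked, yet effectiveness is tested at two-sided 0.1 per test and a conclusion on the better regimen is promised

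*Protocol article*

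**What the plan says.** All references are to the protocol article.

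- **Outcomes (2.10).** "There will be no separation between primary and secondary outcomes since it is an exploratory study to evaluate the independent effectiveness of acupuncture". The sentence adds that outcome data are being collected for further study.
- **Hypotheses (2.2).** The first is directional: "Acupuncture treatment will mitigate pruritus and other symptoms of AD and will improve quality of life in patients with AD, compared with sham acupuncture". The second is that three sessions a week do better than two.
- **Significance level.** Section 2.11.1: "The statistical significance level will be set at 0.1 considering the applied small size". Section 2.11.2: "The data will be analysed with a *p* = 0.1 (two-sided) statistical significance level", with 90% confidence intervals. The two statements agree; the 0.05 level mentioned there belongs to a later trial.
- **Analyses (2.11.2).** "The effectiveness of the intervention will be provided by examining changes in outcome measures between baseline and end of treatment and through the follow-up period", by repeated measures ANOVA and chi-square. VA1 is then compared with VA2 by Mann-Whitney on itch VAS and SCORAD. The better of the two verum arms is compared with sham in the same manner.
- **Use of the results.** Section 2.10.14 also takes the better verum arm into the microRNA comparison with sham. The Discussion says: "Our study results will elucidate which regimen produces maximal effectiveness and which schedule participants prefer".
- **Size (2.11.1).** "A total of 30 individuals with AD and 20 healthy controls will be recruited during the study period". The patients are allocated 1:1:1, with 20% dropout expected.

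**The concern.** The absence of a ranking is a stated choice, not a detail left to an unseen analysis plan. An exploratory study may leave its outcomes unranked if it reports only estimates. This one also sets directional hypotheses and a significance level, and it announces a conclusion about regimens. Nothing says that the p-values are descriptive, and no single test owns the 0.1.

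Two things are at stake. First, a statement that acupuncture beat sham, or that one schedule beat the other, could rest on whichever scale or visit happened to cross 0.1. Second, the better regimen is an input to other planned steps (the sham comparison and the microRNA analysis), and no outcome or time point defines it. If itch VAS and SCORAD point to different arms, the choice would be made after the data are seen.

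The ANOVA is open in a similar way. Its time term and its group-by-time term answer different questions, and the text does not say which one is evidence of effect.

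**Working it through.** **Inputs from the article.** 30 patients in three arms give 10 per arm; with 20% dropout, 10 × (1 − 0.20) = 8. The level is two-sided 0.1. The pairwise tests named are 2 outcomes × 2 contrasts = 4 at one time point, or 8 if weeks 4 and 8 are both tested. Five clinical scales (itch VAS, SCORAD, EASI, POEM, DLQI) are measured at baseline, weeks 1 to 4 and week 8. The article states no familywise error rate, so there is no figure of its own to reproduce.

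**Assumptions (not in the article).** Normal scores; correlation between outcomes 0.3 to 0.8; correlation between visits 0.5, which also gives 0.5 between the week 4 and week 8 changes; the better verum arm picked on mean itch VAS change at week 4.

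**Step 1, one test.** The exact two-sided Mann-Whitney test rejects at U ≤ 27 with 10 per arm (true level 0.089) and at U ≤ 15 with 8 per arm (0.083).

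**Step 2, benchmark for independent tests.** 1 − 0.9^4 = 0.34 for four tests and 1 − 0.9^8 = 0.57 for eight. The actual tests are correlated and slightly conservative, so the true rates are lower.

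**Step 3, simulation with no true effect.** 40,000 trials per setting, counting at least one significant result in either direction over the named tests:

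| Per arm | Outcome correlation | Week 4 only | Weeks 4 and 8 |
|---|---|---|---|
| 10 | 0.3 | 0.288 | 0.465 |
| 10 | 0.5 | 0.274 | 0.448 |
| 10 | 0.8 | 0.239 | 0.401 |
| 8 | 0.3 | 0.270 | 0.443 |
| 8 | 0.5 | 0.258 | 0.426 |
| 8 | 0.8 | 0.230 | 0.385 |

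A single test (itch VAS, week 4, better verum arm against sham) gives 0.08 to 0.09 in the same simulation.

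**Step 4, adding the ANOVA.** If the repeated measures ANOVA is read as a group-by-time test on each of the five scales over six visits, and its results are added to the named tests at weeks 4 and 8, the rate is 0.47 to 0.64 over the settings, or roughly one half. That reading is an assumption.

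**Step 5, disagreement about the better regimen.** With equally effective regimens and outcome correlation ρ, two outcomes favour different arms with probability 0.5 − arcsin(ρ)/π. This is 0.403 at ρ = 0.3, 0.333 at ρ = 0.5 and 0.205 at ρ = 0.8.

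**Step 6, the time term.** Suppose all three arms, sham included, improve by 0.5 SD of change (an assumption). A paired t approximation with n = 30 has noncentrality 0.5 × √30 = 2.74 on 29 degrees of freedom. At two-sided 0.1 it is significant in about 85% of trials (0.848), with no difference between arms.

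**The case against.** The strongest defence is that the exploratory status is substantive. Section 2.1 lists finding suitable outcome measures as an aim, the Discussion asks whether the treatment warrants further study, effect sizes feed a later sample size calculation, and 90% confidence intervals are planned. Leaving outcomes unranked is consistent with that. This stands as a reason not to demand formal multiplicity control. It does not cover the directional hypotheses, the significance level or the regimen conclusion.

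Several stronger readings are tempting, and the article does not support them:

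- **Pairwise tests on all five scales.** A reader might infer Mann-Whitney tests on every scale at weeks 4 and 8, for which simulated rates reach 0.51 for verum against sham and 0.72 with both contrasts (10 per arm, correlation 0.5, verum arm fixed in advance). Section 2.11.2 names only itch VAS and SCORAD for these tests, so those rates describe a plan that was not written.
- **No contrasts named.** Two contrasts are named. What is missing is which of them, if either, is decisive.
- **Significance decides the next trial.** Nothing says that crossing 0.1 selects the regimen or outcome for the main trial.
- **The time term is the planned evidence.** The article does not say so, and section 2.2 frames effect against sham. This is an ambiguity that one sentence would close.

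The rates also count sham beating verum. If only results favouring the better verum arm over sham on the two named scales are counted, the same simulation gives 0.11 to 0.13 at week 4 and 0.17 to 0.20 over both times. Itch VAS is a component of SCORAD (2.10.2), so the higher correlations, and therefore the lower rates, may be nearer the truth.

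**Conclusion.** The concern holds in this form: outcomes are expressly unranked, no time point or contrast is decisive, and effectiveness is nevertheless tested at 0.1 and a regimen conclusion promised.

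For the tests the article names, a nominally significant result with inert acupuncture has probability about 0.23 to 0.29 at week 4 and 0.38 to 0.47 with week 8 added. That is roughly three to five times the rate for one test. A figure near one half needs the assumed group-by-time ANOVA on all five scales. All these rates rest on assumed correlations and count either direction and both contrasts; biomarkers and the other questionnaires are left out.

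The undefined choice of the better regimen is a separate defect. It holds whatever view one takes of multiplicity in a feasibility trial. The point should be corrected, but it is one of wording and pre-specification, not of design.

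**What to change.** 1. **Section 2.10.** Name change in itch VAS from baseline to week 4 as the lead outcome for the verum-sham question, for the VA1-VA2 question and for any choice of the better arm. All other outcomes and time points are supportive. This follows the article's own focus on pruritus.
2. **Section 2.11.2, supportive analyses.** Report them as estimates with the 90% confidence intervals already planned, and call their p-values descriptive. The aim of choosing outcome measures is kept.
3. **Section 2.11.2, verum side.** Define it in advance, for example each verum arm against sham or both pooled, instead of picking it from the same data.
4. **Section 2.11.2, ANOVA.** State that only the group-by-time term, not the time term, counts as evidence of effect.
5. **Discussion.** Replace the promise to show which regimen is most effective with: *will give preliminary estimates of the difference between regimens*.

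A rule that tests VA1 against VA2 only after a significant verum-sham result should not be added. Under the present text it is circular, because the regimens must be compared before the verum arm is known. Power for the first test with a pre-fixed arm would be about 0.26 (true effect 0.5 SD) or 0.49 (0.8 SD) with 10 per arm, and 0.21 or 0.39 with 8 per arm. The rule would therefore block the regimen question in about half to four-fifths of trials (1 − 0.49 = 0.51 to 1 − 0.21 = 0.79) in which acupuncture works to that extent.

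The cost is wording only, with no added patients, visits or data. The small downside is that an effect seen only on another scale, or only at week 8, would be hypothesis-generating.

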#### 2.10.1. SCORAD Index

SCORAD is a widely used tool for assessing severity of AD. The SCORAD evaluates the intensity and extent of affected regions and estimates subjective discomfort such as pruritus and sleep loss symptoms [26–28]. The SCORAD index contains 6 items to evaluate AD intensity: erythema, excoriation, oedema or papulation, lichenification, oozing or crust, and dryness. The extent of the lesions is evaluated as a percentage of entire external surface of the human body with the rule of nine. The SCORAD grades the intensity and extent of affected skin and the participant rates their subjective symptoms with VAS (0 = no itch or sleep loss, to 10 = worst imaginable itch or sleep loss).

#### 2.10.2. Itch VAS

The itch VAS is one of the components of the SCORAD index, and it will be particularly applied to assess the severity and reduction of pruritus in this trial. Participants whose itch VAS score is less than 30 or higher than 80 will be excluded because we assumed that they will have lower desire for antipruritic therapy or need more potent treatment [29].

#### 2.10.3. EASI Score

The Eczema Area and Severity Index (EASI) is a validated instrument measuring AD severity [28, 30]. Questions are specific to four body regions (head and neck, trunk, upper extremities, and lower extremities) and four symptoms (erythema, oedema/papulation, excoriation, and lichenification).

#### 2.10.4. POEM

The Patient Oriented Eczema Measure (POEM) is a useful, 7-item tool for monitoring AD severity, which focuses on participant-reported symptoms and illness. Scores range from 0 to 28, and it is suitable for administration in the outpatient clinic or in the clinical trial setting [28, 31].

#### 2.10.5. DLQI

The Dermatology Life Quality Index (DLQI) is a compact questionnaire which is applicable to individuals with any skin disease. It measures the influence of AD on participant's life over the previous 7 days. It consists of 10 questions with Likert-type responses and its score ranges from 0 to 30; higher scores imply greater influence on health-related quality of life [10, 32].

#### 2.10.6. TCS Use

Only Lidomex (prednisolone valeroacetate) will be permitted as a rescue medicine for severe pruritus, by consensus of the study KMD and the pharmacist at Kyung Hee University Korean Medicine Hospital. Participants will be instructed to apply TCS according to the fingertip method: the ointment will be applied on the surface area of one palm with amount from the tip of index finger to the distal skin crease [10].

Participants using TCS will report the amount used, frequency, and affected regions weekly during this trial. Ointments will also be weighed weekly before being dispensed and then again at the end of this study in order to evaluate the amount of TCS used [33].

#### 2.10.7. AD Pattern Questionnaire

To reflect a unique point of view on pattern diagnosis in Traditional Korean Medicine in an objective manner, we adopted the AD pattern questionnaire [34]. Participants with AD will be categorised as either excess or deficient syndrome by answering 20 “yes or no” type questions about their AD symptoms and pulse/tongue diagnoses. A KMD will make diagnoses based on the categorisation.

#### 2.10.8. Cold-Heat Questionnaire

Identifying cold and heat pattern is a relatively obvious and definite factor of diagnosis in Traditional Korean Medicine and the usual cold-heat pattern of patients plays an important role in choosing treatment modalities and establishing treatment plans [35]. We will use the questionnaire of cold-heat pattern identification based on usual conditions and signs. By assessing their usual cold-heat pattern, participants will be classified into one of four categories: Cold; Heat; No Cold-Heat; and Cold-Heat complex [36].

#### 2.10.9. PPT

Abdominal examination has been one of the characteristic methods for diagnosis, choosing a therapy, and predicting prognosis in Traditional Korean Medicine [37]. We will utilise an algometer to standardise and quantitatively describe the abdominal examination [38]. Using an algometer (Wagner Instruments, Greenwich, CT), one operator will apply pressure to 3 acupoints (CV17, CV12, and ST25) vertically against the surface. Pressure will be applied at a rate of 1 kg/cm^2^/sec and participants will be instructed to report the beginning of pain by saying “stop” immediately after the perception of pain is transferred from pressure. The examiner will immediately stop pressing and record the pressure pain threshold (PPT) value. The maximum PPT will be limited to 8 kg/cm^2^ in order to prevent distorted measures. At each assessment, PPT will be measured three times with the intervals of 1 minute [38, 39].

#### 2.10.10. CES-D

Since it has been reported that depression is strongly associated with AD, evaluating depressive symptoms of the patient is highly recommended [40, 41]. The CES-D is a reliable tool for nonpsychiatric populations and the validated Korean version will be used for this trial [42, 43].

#### 2.10.11. STAXI

It is widely reported that AD patients have a higher risk of depressive symptoms and a reduced capacity to cope with stress or anger [41, 44]. With a suggested relationship between depression and anger suppression in AD patients [41], assessing the anger trait will be valuable to interpret outcomes in the context of participants' responses.

STAXI is a validated measure for assessing the experience, expression, and control of anger. It has 3 subscales such as trait anger, anger-inside (anger suppression), and anger-outside (anger expression) and consists of a total of 44 questions [45]. The validated Korean STAXI will be applied for this trial [46].

#### 2.10.12. Credibility Test

To assess the credibility of the acupuncture treatment used in this study, participants will complete the credibility questionnaire at baseline, at 4 weeks (after the termination of treatment period), and at 8 weeks (after the end of follow-up period) [47, 48].

